#### Laboratory tests for the assessment of IG count, neutrophil phagocytic activity and cfDNA levels

Patient samples will be analysed at the University of Birmingham laboratories based at the QEHB. Samples will be accompanied by a pseudonymous form with no patient identifiable data. IG counts and neutrophil phagocytic activity will be assessed on the day of patient sampling, with blood samples processed immediately on their arrival into the laboratory. Assays for the measurement of cfDNA levels will be performed in two batches, details of which are outlined below.

##### IG counts

Whole blood cell counts will be performed on citrated whole blood using a Sysmex XN-1000 haematology analyser (Sysmex UK, Milton Keynes, UK), which defines IGs as promyelocytes, myelocytes and metamyelocytes within the white cell differential channel. Instrument performance will be ensured by daily measurement of quality control material (XN Check) and via participation in an external quality assurance scheme (UKNEQAS, Watford, UK).

##### Neutrophil phagocytic activity

Neutrophil phagocytosis of fluorescently labelled opsonised *Escherichia coli* will be measured on heparinised whole blood using the commercially available PhagoTEST assay (BD Biosciences, Oxford, UK). To account for postburn leucocytosis, patient’s white cell counts will be normalised to those of HCs in order to ensure consistent leucocyte to bacteria ratios across all assays. By ‘quenching’ the fluorescent signal emitted from bacteria bound to the external plasma membrane of neutrophils, inclusion of a trypan blue staining step within this assay ensures that the fluorescent signal measured by flow cytometry is derived only from phagocytosed bacteria.

For the acquisition of raw data, a single flow cytometry template with specified gating plots and event limits will be used by all researchers analysing patient and HC blood samples. Gated based on their distinctive sideward scatter/forward scatter properties, a total of 10 000 neutrophils will be analysed and data relating to both the percentage of cells that have performed phagocytosis (% phagocytosis) and their mean fluorescence intensity (an indicator of the number of ingested bacteria per neutrophil) will be recorded. This information will then be used to calculate neutrophil phagocytic capacity using the following equation: (% phagocytosis/100) × mean fluorescence intensity.

Prior to flow cytometric analysis of all patient and HC blood samples, BD CS&T beads (BD Biosciences) will be run on the flow cytometer. These beads will ensure a standardised method of quality control will be performed on our instrument in respect to its optics, electronics and fluidics.

##### CfDNA measurements

The concentration of total cfDNA), mitochondrial-derived DNA (mtDNA) and nuclear-derived DNA (nDNA) will be measured in platelet-free plasma (PFP) prepared from citrate anticoagulated blood samples. PFP will be stored at −80°C prior to analysis, which will be performed in two phases (phase 1: analysis of samples collected 1–28 days postburn; phase 2: analysis of samples collected at months 3–24 postburn).

Total cfDNA concentrations will be determined in duplicate PFP samples using an in-house SYTOX Green dye based fluorometric assay as described previously.^18^ Included within each assay will be: (1) a λ-DNA standard curve (0–1000 ng/mL) for calibration, (2) PFP samples from HCs, stored under the same conditions as our patient samples, to serve as reference values and (3) a ‘buffer only’ negative control. The mean fluorescence value derived from the negative control will be subtracted from all HC and patient data prior to the calculation of DNA concentration. A selection of patient and HC PFP samples will be analysed across assays to allow for the calculation of interassay and intra-assay coefficients of variation, which currently stand at 5.3% and 5.1%, respectively. Analysis of 32 PFP samples using our in-house assay quantified cfDNA to concentrations that were comparable to those measured using a CE-marked commercially available assay (Trillium Diagnostics; Spearman’s R=0.78, p<0.0001).

Using primer sets specific for the genes encoding cytochrome b and β-globin, real-time PCR will be performed to determine the concentration of mtDNA and nDNA, respectively.^18^ Included within each assay will be: (1) standard curves generated using DNA isolated from purified mitochondria and nuclei to enable quantification of mtDNA and nDNA concentrations, (2) DNA isolated from HC PFP samples, stored under the same conditions as our patient samples, to serve as reference values and (3) a ‘buffer only’ negative control. PFP samples from a selection of HCs and patients will be analysed across assays to allow for the calculation of interassay and intra-assay coefficients of variation. Our cytochrome b and β-globin primer sequences have no significant homology with DNA found in any bacterial species according to information provided by the Basic Local Alignment Search Tool.

#### Outcomes

In line with our original study,^18^ sepsis will be defined according to the 2007 ABA diagnostic criteria for sepsis in burns.^9^ A diagnosis of sepsis will be made when >3 of the following criteria are met along with a positive bacterial culture or when a clinical response to antibiotics is detected:

Temperature (>39^°^C or<36^°^C).Progressive tachycardia (adults, >110 beats per minute; children, >2 SD above age-specific norms (85% of age-adjusted maximum heart rate)).Progressive tachypnoea (adults, >25 breaths per minute not ventilated or minute ventilation >12 L/minute for ventilated patients; children, 2 SD above age specific norms (85% of age-adjusted maximum respiratory rate)).Thrombocytopenia (Adults, platelet count <150x10^9^/L (this will not be applied until 3 days after initial resuscitation; children, <2 SD below age-specific norms).Hyperglycaemia (untreated plasma glucose >200 mg/dL or insulin resistance as defined by either (1) >7 units of intravenous insulin per hour or (2) significant resistance to insulin (>25% increase in insulin requirements over 24 hours).Feed intolerance (inability to continue enteral feeding >24 hours defined using (1) abdominal distension, (2) enteral feeding intolerance (adults, two times the feeding rate; children, residual >150 mL/hour) or (3) uncontrollable diarrhoea (>2500 mL/day for adults or >400 mL/day in children).

Blood cultures will be taken whenever the temperature of a patient is >38.5°C and they will be acquired from a clean venepuncture site where possible using a sterile technique. If such a site is not accessible, due to the patients injuries, then blood cultures will be obtained from a pre-existing central venous catheter. The results will be interpreted following detailed discussions with the microbiology team.

Burn wound infection/sepsis will be documented in the CRF after assessment by a senior surgeon together with information attained from the relevant microbiology wound swabs/tissue biopsies. In addition, time to 95% wound healing will be documented as an overall measure of the patients care and for wound related complications such as wound sepsis.

Alongside recording data that will allow for the diagnosis of sepsis using the 2007 ABA consensus, clinical data will be collected from all patients so that the following clinical scores can be calculated: (1) Early Warning Score, (2) multiple organ dysfunction syndrome, (3) Sequential Organ Failure Assessment score, (4) Marshall Score and (5) SIRS Score. Comprehensive daily records of different scores will allow for more detailed analyses should a sepsis score for burns patients be validated in the future. This is particularly important for children, given that applying the ABA consensus score is challenging in this patient population, where organ dysfunction may be more indicative of sepsis.^31^

### Data analysis

Data will be assessed for normality using the Shapiro-Wilk test. Normally distributed data will be presented as mean values with SD. Non-normally distributed data will be presented as median values with IQR. Comparisons of baseline continuous data (eg, demographics, injury characteristics) between two groups (eg, HCs vs burns patients or septic vs non-septic patients) will be conducted using an unpaired Student’s t-test for normally distributed data or the Mann-Whitney U test for non-normally distributed data. Categorical baseline data will be compared using a χ^2^ test. Laboratory data obtained from HCs and patients across the different sampling time points will be compared using either a one-way analysis of variance with a Dunnett post hoc test for normally distributed data or a Kruskal-Wallis test with a Dunns post hoc test for non-normally distributed data. A p <0.05 will be considered statistically significant.

We will determine in how many participants the measurements of neutrophil phagocytic capacity, plasma cfDNA levels and IG count on day 1 of injury predicted a diagnosis of sepsis. This proportion will be reported along with 95% CIs calculated by binomial exact methods. The accuracy of this day 1 biomarker model will be determined through standard estimates of sensitivity, specificity, predictive values and likelihood ratios, with 95% CIs. We will investigate the value added by this day 1 biomarker test when compared with information obtained from other potentially informative sets of biomarkers (eg, revised Baux score). These combinations of tests will be assessed using logistic regression models. Using multivariable logistic regression analysis, we will also generate predictive probabilities for various combinations of these candidate biomarkers. This logistic modelling will aim to derive a prognostic regression function (ie, probability of sepsis) using the day 1 values of each candidate biomarker and other demographic or burn-related variables. Models of varying complexity may be compared through ROC analyses. Longitudinal data collection will enable us to examine how the performance of these models change over time. Limitations associated with the logistic regression approach lie mainly in its generalisability to other data sets. Thus, techniques such as bootstrapping to enhance generalisability will be applied for model validation. In sensitivity analyses, missing data will be estimated by multiple imputation and maximum-likelihood methods, as appropriate, in order to explore the potential bias and reduced statistical power associated with listwise deletion.

Serial sampling will allow for repeated measures analyses of our candidate biomarkers, enabling us to model their kinetics over time and examine how this differs between septic and non-septic patients. For the analysis of longitudinal data, continuous outcomes will be analysed using linear regression to compare the septic and non-septic groups, with mean differences and 95% CIs reported. For other outcomes, analysis of daily measurements will be performed using generalised linear mixed models to account for the hierarchical structure of the data. Summaries of model output will be provided with model effects presented both as estimates with associated 95% CIs and also, where appropriate, as plots to visualise the time course of fitted outcomes.

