#### Exclusion

Associated multiple injuries with an injury severity score (ISS) >25.Decision not to treat due to the severity of the injury. This decision will be made at the time of hospital admission.Patients with chemical or deep electrical burns.Patients receiving glucocorticoid treatment.Patients with active malignancy.Patients with multiple limb amputations (amputations would skew the calculation of TBSA scores).Patients with known long-term infections (eg, hepatitis B and C, HIV).

Alongside burns patients, a maximum of 100 adults and 10 children will be recruited to serve as a cohort of age-matched healthy controls (HCs), with the only exclusion criterion being current treatment with anti-coagulant medication or an acute infection.

Adult HCs can be recruited from age 16 years, with no upper age limit. Enrolment of up to 100 healthy adults will enable us to undertake diverse sampling of the adult population, allowing us to control for as many of the variations that encompass this broad age range as possible (eg, general physical condition, concurrent medical conditions and drug therapies, past exposure to disease or injury and different degrees of physiological ageing). Adult HC volunteers will be recruited through advertisements disseminated at the QEHB, BCH, the University of Birmingham campus and via online newsletters. When an expression of interest for study participation is received by the burns research team, a patient information leaflet (PIL) detailing the conditions of the study will be sent to the volunteer. All subjects who receive a PIL will be recorded on a screening log that will be held in the site file at the QEHB. Adult volunteers will attend the QEHB to participate in the study.

The paediatric HC group will consist of children undergoing elective plastic surgery procedures at the BCH. These surgeries will include mole removal, correction of prominent ears, revision of plastic surgery and cosmetic type surgery. In terms of age range and a lack of other health conditions or ongoing medical treatments, paediatric HCs will represent a more homogeneous cohort when compared with our adult HC group. Thus, we expect to observe much less variability in the baseline immune profiles of paediatric HCs. This factor, combined with the complexity of recruiting paediatric HCs, is the reasoning behind our decision to enrol a maximum of 10 healthy paediatric volunteers into the SIFTI-2 study.

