### Sample size

The sample size for this study is based on data collected from adult patients recruited into the SIFTI-1 study.^18^ Of the 57 adult burns patients who survived for at least 7 days following study enrolment, 35 developed sepsis, equating to a prevalence of 61%. Of these, 33 patients, with a TBSA burn ≥15%, had measurements of neutrophil phagocytic capacity, plasma cfDNA levels and IG count recorded on day 1 of injury. These data provided good discriminatory power to identify septic patients, with logistic regression modelling providing an area under the ROC of 0.935. Adjusted for shrinkage following internal bootstrap model validation to account for potential overfitting, this model exhibited a specificity of 0.75 and a sensitivity of 1.00. Based on this information, we computed the sample sizes required to estimate a 95% CI for sensitivity (with a maximum width of 10%) and for specificity (with a maximum width of 20%) for prevalence rates of sepsis ranging from 50% to 70%. Assuming a prevalence of sepsis of at least 60% and that the ‘true’ sensitivity is at least 90% and the ‘true’ specificity is at least 70%, these analyses revealed a total of 220 patients would allow us to reliably rule out a sensitivity less than 84% and a specificity of less than 59%. Assuming that the 10% drop-out rate we recorded for patients over the first 7 days of the SIFTI-1 study holds true for this follow-on study, then a total sample size of 245 burns patients, which includes both adult and paediatric age groups, is required for the SIFTI-2 study.

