### Data collection and patient outcomes

In this prospective longitudinal study, data will be acquired from burns patients at the following 19 postinjury time points: days 1–14, day 28 (±3 days) and months 3, 6, 12 and 24 (±2 weeks). Patient enrolment into the study began on 27 November 2016, with an estimated end date of December 2025.

Across the settings of paediatric and adult burns, a significant number of studies have undertaken serial blood sampling to investigate the short (<1–7 days), medium (8–34 days) and long (35–1100 days)-term inflammatory response to thermal injury and its relationship with patient outcome.^22–28^ In contrast, very little data currently exist on the acute and long-term effects of thermal injury on the immune system.^19 24 29^ Thus, generating data on the kinetics of the immune response to burn injury via serial sampling in both our adult and paediatric cohorts will allow us to not only establish how long burn-induced changes in immunity persist for, when compared with HCs, but also compare the immune response of septic and non-septic burns patients over time. Generating and interrogating such novel data may provide mechanistic insights into the long-term health complications reported by survivors of burn trauma, which include an increased susceptibility to respiratory infections.^30^

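### The comparison of healthy controls with serial patient samples uses one-way ANOVA or Kruskal-Wallis, which treats up to 19 samples from the same patients as independent groups

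*Protocol article*

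**What the plan says.** Under Data collection and patient outcomes, "data will be acquired from burns patients at the following 19 postinjury time points": days 1 to 14, day 28, and months 3, 6, 12 and 24. One stated purpose of this serial sampling is to "establish how long burn-induced changes in immunity persist for, when compared with HCs".

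The Data analysis section names the test for that comparison: "Laboratory data obtained from HCs and patients across the different sampling time points will be compared using either a one-way analysis of variance". Dunnett's test follows the ANOVA; where data are not normal, Kruskal-Wallis followed by Dunn's test takes its place. The section then sets the significance level: "A p <0.05 will be considered statistically significant". No patient effect, repeated-measures ANOVA or robust variance is named for it.

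The controls are described under Exclusion: "a maximum of 100 adults and 10 children will be recruited to serve as a cohort of age-matched healthy controls".

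Later in Data analysis, repeated-measures analyses are announced for how marker kinetics differ between septic and non-septic patients. Continuous longitudinal outcomes there get linear regression. Generalised linear mixed models, with the hierarchical structure given as the reason, are kept for other outcomes. Healthy controls do not appear in that paragraph.

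**The concern.** Dunnett's procedure compares several groups with one control. The natural reading is therefore that healthy controls are the reference and each sampling time is a separate group. Up to 19 of those groups are then the same people. One-way ANOVA and Kruskal-Wallis assume independent groups, so their reference distributions do not apply.

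Two things are at stake for the persistence question. A small lasting change may be missed because the test is too strict. A late difference may also appear, or disappear, because of which patients remain under follow-up, since each time point is analysed without the same patients' earlier values.

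**Working it through.** **The plan's own figures.** The article gives no figure for the control comparison. Its sample size does reproduce: 220/0.9 = 244.4, so 245. With 60% prevalence, 220 × 0.6 = 132 septic and 88 non-septic patients. Exact 95% lower limits are 83.7% (119/132) for sensitivity and 58.6% to 59.8% (61 or 62 of 88) for specificity, against the stated 84% and 59%. None of this depends on the ANOVA.

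**Inputs.** From the article: 220 evaluable patients, 19 time points, at most 100 + 10 = 110 controls, alpha 0.05. Assumed, because the article gives no values: one sample per control, two-sided tests, normal data with equal SDs, no missing data (except in step 5), and exchangeable within-patient correlation ρ of 0.3, 0.5 or 0.7.

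**Step 1: why the overall test is too strict.** Differences between time points have variance reduced by the factor (1 − ρ), but the one-way F divides by the full variance σ². With 20 groups and 110 + 19 × 220 = 4,290 samples, the between-group mean square has 19 df. Of these, 18 df (between times) have expectation (1 − ρ)σ². The remaining 1 df (controls versus all patient samples) has expectation (110 × 4,180/4,290) × [1/110 + (1 + 18ρ)/4,180]σ².

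| ρ | 18(1 − ρ) | 1-df term | Expected F ≈ sum/19 |
|---|---|---|---|
| 0.3 | 12.6 | 1.14 | 0.72 |
| 0.5 | 9.0 | 1.23 | 0.54 |
| 0.7 | 5.4 | 1.32 | 0.35 |

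Independent groups would give about 1. The 5% critical value, F with 19 and 4,270 df, is about 1.59.

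**Step 2: simulated error under no difference** (1,500 to 2,000 runs per setting).

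| ρ | One-way F | Repeated-measures test | Dunnett family-wise |
|---|---|---|---|
| 0 | about 5% | 5.1% | 5.4% |
| 0.3 | 0.2% | 4.7% | 2.9% |
| 0.5 | 0.0% | 5.1% | 3.0% |
| 0.7 | 0.0% | 5.1% | 2.1% |

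Kruskal-Wallis behaves about the same as the F test. Under AR(1) correlation of 0.8 the overall error is 2.2% with 14 days and 3.7% with 19 time points; Dunnett's is 2.7%.

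**Step 3: control-versus-day contrasts.** Controls and patients are different people, so each contrast has standard error √(1/110 + 1/220) = 0.117 SD whatever ρ is. Single unadjusted contrasts therefore stay near 5%. Only the joint critical value is off: Dunnett uses about 2.78, where 2.69, 2.60 and 2.47 would suffice at ρ = 0.3, 0.5 and 0.7. For a true difference of 0.35 SD, 0.35/0.117 = 3.00. Power per time point is then about Φ(3.00 − 2.78) = 59%, against about 62%, 65% and 70% with the correct values. Simulation gives 59% against 63%, 66% and 70%.

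**Step 4: power of the overall test.** For a constant 0.35 SD difference from controls at all times, one-way power is 32%, 20% and 13%, against 40%, 37% and 34% for the repeated-measures test. For a linear drift over 14 days, one-way power is about 91% to 96% at 0.3 SD, but only about 10% to 41% at 0.2 SD. A repeated-measures F test of the 0.2 SD drift has 91% power at ρ = 0.5 and 99.6% at ρ = 0.7.

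**Step 5: loss to follow-up and unequal SDs.** Assume about 40% retention, with the log-odds of retention rising by 1 per SD of the early value, and no true late difference. The late control contrast is then biased by 0.15, 0.24 and 0.34 SD at ρ = 0.3, 0.5 and 0.7, and its unadjusted type I error is 19%, 40% and 70%. A likelihood estimate that uses the early values has bias of about 0. Separately, at ρ = 0.5 with complete data, Dunnett's family-wise error is about 12% if the control SD is 1.5 times the patient SD, and about 0.2% if it is half.

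**The case against.** The strongest defence is that the contrasts which answer the persistence question are nearly sound. Each control-versus-day contrast compares different people, and with complete data and equal SDs its error is near nominal. This stands, and it limits the finding: the large distortion is in the overall test, which does not itself say how long a change lasts.

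A reader might infer from the near-zero null rejection rate that the test has almost no power for change over time. That does not follow. Power is about 91% or more for a 0.3 SD drift, and the serious loss is confined to smaller changes. Nor does the error run mainly towards false positives; with complete data and equal SDs it runs the other way.

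A reader might also infer that the comparison is confounded by age, since controls include at most 10 children. The article does not say that adults and children are pooled. It describes separate adult and paediatric control groups, each with its own recruitment route and rationale, and it gives no paediatric share of patients from which a bias could be calculated. Age adjustment is a sensible part of the repair, not a demonstrated error.

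The sizes depend on the assumed correlation, and AR(1) gives milder results. This also stands.

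Finally, the article plans multiple imputation and maximum-likelihood sensitivity analyses for missing data. They follow the day 1 prediction models and are not tied to the control comparison, so they do not settle the attrition point. Nor is this detail left to an analysis plan: the article names both the test and its post hoc procedure.

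**Conclusion.** The point holds. The named test does not fit the stated design, and nothing elsewhere in the article replaces it for the control comparison. The loss is large for the overall test under exchangeable correlation and modest for the Dunnett contrasts.

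The more serious risk to late time points is selective follow-up. Its size here rests wholly on an assumed retention pattern, and its direction would depend on who is lost. Correlations, SD ratios and retention are all assumptions, so the magnitudes are illustrative. The violation of independence is not.

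The consequence is confined to the secondary kinetic aim. The primary day 1 sepsis objective and the total of 245 are untouched. The wording should be changed before analysis, but it does not threaten the study's main result.

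**What to change.** In Data analysis, replace the one-way ANOVA/Dunnett and Kruskal-Wallis/Dunn sentence with one linear mixed model per marker, transformed if skewed:

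- healthy control as the reference level and each sampling time as a factor level;
- a patient random effect or a within-patient covariance; a covariance that lets correlation fall with the time gap is safer than a random intercept alone;
- separate variances for controls and patients;
- age and sex as covariates.

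Report contrasts of each time with control from that model, adjusted for multiplicity using the model's own covariance. Fitting all available samples lets earlier values inform later means when follow-up depends on them. It does not protect against loss that depends on unobserved values, which the text should acknowledge.

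Use the same approach for the continuous longitudinal comparison of septic and non-septic patients, which now names plain linear regression.

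The cost is analysis wording only. Age and sex are in Table 1 for patients, and date of birth and gender are recorded for controls. No extra samples or participants are needed.

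### A single Dunnett or Dunn comparison across all time points gives the month 3–24 contrasts with healthy controls an error term set mainly by the acute phase

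*Protocol article*

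**What the plan says.** The Data analysis section of the protocol article states the scope of the test: "Laboratory data obtained from HCs and patients across the different sampling time points will be compared". The method is a "one-way analysis of variance with a Dunnett post hoc test for normally distributed data or a Kruskal-Wallis test with a Dunns post hoc test", and the choice between the two follows from an opening rule: "Data will be assessed for normality using the Shapiro-Wilk test". On significance it says "A p <0.05 will be considered statistically significant". It names no unequal-variance version and no transformation.

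Data collection and patient outcomes lists 19 sampling times. Days 1–14 and day 28 make 15, and months 3, 6, 12 and 24 make four. The same section gives serial sampling the purpose to "establish how long burn-induced changes in immunity persist for, when compared with HCs". For controls, the Exclusion section says "a maximum of 100 adults and 10 children will be recruited".

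The longitudinal models later in Data analysis are described for septic against non-septic patients. The Dunnett or Dunn sentence is therefore the only named test of patients against HCs over time.

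**The concern.** Classical Dunnett divides every contrast by one residual SD estimated from all groups. Dunn compares mean ranks taken from one ranking of all groups together. Neither lets the contrast of month 24 with HCs rest on those two groups alone.

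Fifteen of the 19 patient groups come from days 1–28, and they will also be the largest. If acute values are more spread out, Dunnett gives the late contrasts too large a standard error. If acute values are also displaced from HC values, Dunn squeezes late and HC values into a narrow band of ranks. If acute values are less spread out, Dunnett's standard error for the late contrasts is too small.

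How long immune changes last is read from exactly these late contrasts. A persisting change could be missed, or a false one declared, because of data from other time points. The fault would remain if every time point came from different patients, so it is separate from the repeated sampling of the same people.

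**Working it through.** **The plan's own figures.** The article states no power, SD or expected difference for the HC comparison, so there is nothing to reproduce for it directly. The only sample-size figure concerns sensitivity and specificity, and it reproduces. 220 × 0.6 = 132 septic and 88 non-septic patients. Exact lower 95% limits are 83.6–83.7% at 90% sensitivity and 59.3–59.8% at 70% specificity, against the stated 84% and 59%. 220/0.9 = 244.4, hence 245. It is used here only as the source of the 220.

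**Inputs.** From the article: 19 time points, at most 100 adult and 10 child HCs, 220 evaluable patients, significance level 0.05 (taken as two-sided). Assumed: 100 HCs, 220 patients on each of days 1–14, 150 on day 28, 100 at each of months 3–24, independent samples, HC and late SD = 1, acute shift 1.5 SD. The ratio r of acute to late SD is varied.

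**Dunnett: pooled SD.** Acute observations: 14 × 220 + 150 = 3,230. HC and late observations: 100 + 4 × 100 = 500. Total 3,730, of which 87% are acute.

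Pooled SD = √[(3,230 r² + 500)/3,730]:
- r = 0.7: 0.747
- r = 1: 1.000
- r = 1.5: 1.443
- r = 2: 1.897

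**Dunnett: power at month 24.** The statistic divides the difference by pooled SD × √(1/100 + 1/100) = pooled SD × 0.1414. The true standard error is 0.1414. For a true difference d the statistic therefore has mean d/(0.1414 × pooled SD) and SD 1/(pooled SD). The simulated Dunnett critical value for these group sizes is 2.80.
- r = 2, d = 0.5: mean 1.864, SD 0.527; power = P(Z > (2.80 − 1.864)/0.527) = P(Z > 1.78) = 4%.
- r = 1.5, d = 0.5: mean 2.450, SD 0.693; P(Z > 0.51) = 31%.
- r = 1, d = 0.5: mean 3.536, SD 1; P(Z > −0.74) = 77%.
- r = 2, d = 1.0: mean 3.728, SD 0.527; P(Z > −1.76) = 96%.
- Two groups' own SD, Bonferroni for 19 (critical value 3.01), d = 0.5: P(Z > 3.01 − 3.536) = 70%.

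**Dunn: the joint ranking.** The expected difference in mean rank, as a fraction of N, is the difference between the two groups in the probability of exceeding a randomly chosen pooled observation. Take r = 1, shift 1.5, d = 0.5.
- Against acute observations: Φ(−1.0/√2) − Φ(−1.5/√2) = 0.240 − 0.144 = 0.095.
- Against HC and late observations: Φ(0.5/√2) − 0.5 = 0.138.
- Weighted: 0.095 × 3,230/3,730 + 0.138 × 500/3,730 = 0.101.
- Dunn's standard error on this scale is √(0.02/12) = 0.0408, so the expected z is about 2.48 against a critical value of 3.01. With no acute shift it would be 0.138/0.0408 = 3.39.

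A shift alone, without extra spread, therefore moves the expected z from above the threshold to below it.

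**Simulation under the same assumptions (month 24 v HC, acute shift 1.5 SD).**

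| Acute SD ratio | Late difference | Dunnett | Dunn | Two-group Welch or Wilcoxon, Bonferroni |
|---|---|---|---|---|
| 2 | 0.5 SD | about 3% | about 5% | 67–71% |
| 1.5 | 0.5 SD | 31% | 15% | about 64–71% |
| 1 | 0.5 SD | 75% | 27% | about 64–71% |
| 2 | 1.0 SD | 96–98% | 96–98% | near 100% |

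Repeats of the Dunn cell at ratio 1 gave 22–27%, so read it as roughly a quarter. With no acute shift and ratio 1 the methods differ little: 78% Dunnett, 66% Dunn, 70% Welch, 66% Wilcoxon.

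**The opposite case.** At r = 0.7 and no true late difference, Dunnett's statistic has SD 1/0.747 = 1.338. P(|Z| > 2.80/1.338 = 2.09) = 3.6% (about 3% in simulation). The same formula gives 0.5% at equal spread, and two-group Welch at the Bonferroni level gives 0.05/19 ≈ 0.3%.

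**The case against.** Much of the case against stands.

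- **Size.** A reader might infer that persisting changes at months 3–24 will be largely undetectable. The documents do not support that. They give no biomarker SD at any time point, no expected late difference and no retention beyond a 10% loss in the first 7 days. A 1.0 SD late difference stays detectable at ratio 2, and the Dunn loss shrinks with the shift: at equal SDs, power for 0.5 SD is 48% with a shift of 1.0 SD and 65% with 0.5 SD.
- **Direction.** The Introduction describes phagocytosis as impaired after burns. If a suppressed marker varies less in the acute phase, Dunnett errs towards false positives, so loss of power is not the only possible consequence.
- **Reading.** That one test spans HCs and all 19 time points is an inference from the wording. The cfDNA assays run in two phases (days 1–28 and months 3–24), so a phase-wise comparison is conceivable. With HCs and the four late visits only, power for 0.5 SD would be about 85% (Dunnett) and 80% (Dunn), and the fault goes. But the phases are an assay arrangement, and Data analysis does not split the comparison.
- **Normality testing.** A reader might also infer that Shapiro-Wilk over many groups will almost certainly lead to the Dunn route. The article does not say that each group is tested or that one rejection switches the whole analysis, so nothing here rests on that.
- **Left to an analysis plan?** The analysis scale could be. The test itself, however, is named in the article, and it is the test that creates the dependence on acute data.

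**Conclusion.** The point holds in conditional form. On the natural reading of Data analysis, the error attached to each month 3–24 contrast with HCs is set mainly by days 1–28. It is wrong for Dunnett when acute spread differs from late and HC spread. Dunn is distorted by acute level as well as spread.

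Under the stated assumptions the consequence runs from no material loss (no acute shift, equal spread) to near-total loss of power for a 0.5 SD difference (ratio 2). With a smaller acute spread, Dunnett's per-contrast false-positive rate is instead roughly ten times that of Welch (about 3% against about 0.3% at ratio 0.7). Which of these applies to which marker cannot be told from the article.

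The persistence aim in Data collection and patient outcomes is affected. The primary objective is not: prediction of sepsis from day 1 values, and the sample size built on it, do not use the HC tests. The correction is worth making before analysis. Confidence is moderate, because the single joint test is inferred and the variances are unknown.

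**What to change.** Replace the Dunnett or Dunn sentence with one of two options:

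1. At each time point, compare HCs with patients using only those two groups' data: a Welch contrast on a suitable scale (for example log) or a Wilcoxon test, with Holm adjustment over the 19 time points.
2. Take the HC contrasts from a repeated-measures model that includes HCs and allows a separate variance for HCs and for each time point, with adjustment over the 19 contrasts. A model with one common residual variance would keep the fault.

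Fix the method and scale for each marker in advance and do not choose between tests by Shapiro-Wilk. Report each difference with its confidence interval.

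The cost is analysis wording only, with no new data or visits. If all variances are in fact equal, power is slightly lower than with Dunnett: about 70% against 77% in the arithmetic above for a 0.5 SD difference.
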